## Methods

### Study design

A multi-centre parallel-group randomised controlled superiority trial [25] (RCT) with embedded mixed-methods process evaluation, comparing the BOOST pACP program to standard care (control group). Adolescent patients and their parent(s) will be randomised with a 1:1 allocation ratio to the intervention arm or the control arm after baseline assessment. The mixed-methods process evaluation is structured according to the Medical Research Council (MRC) Framework by Moore et al. [26].

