#### Control

The control group will not receive the BOOST pACP program. Adolescents in the hospitals are seen by different oncologists and nurses. Families that are recruited via four participating university hospitals will have access to contact with psychologists whenever they request it. Paediatric ACP is not implemented as standard care within these hospitals. The conversation cards that can be used as a game of quartet at home are offered to the families in the control group after study completion.

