### Recruitment procedures

The recruitment period will be 2 years (2021–2023). We will recruit adolescents via two different streams:
Patients will be recruited in all four participating university hospitals in Flanders, Belgium, via the paediatric oncology wards. Each of the hospital wards will assign one staff member as the main point of contact for the study. The contact person asks each paediatric oncologist to assess which patients would meet the inclusion criteria. The paediatric oncologist or psychologist will ask the parents of these patients whether they would be willing to participate in the study by giving a short explanation and asking whether they agree for a data collector to call them to provide more information about the study. The data collector will then contact one of the parents by phone. If the parent agrees to participate, the data collector will make an appointment with the parent(s) (depending on which parents are considered eligible, see Fig. 1) and the adolescent. During the appointment, the data collector will explain that both parents are encouraged to join the conversation sessions, but that it is not obligatory for both parents to join all conversation sessions of the program to be able to enrol in the study.We will recruit adolescents with cancer and their parent(s) through support organizations that meet the following criteria: 1) they are non-profit; 2) they are based in Flanders or Brussels; 3) adolescents with cancer or their parents are one of their target groups. Organizations are contacted by the researcher ([name]) and are asked to post an open call using a flyer developed by the research team via their newsletters, website and other social media or share this in other ways that are part of their regular channels of communication with their members and network. Adolescents and/or parents can contact the data collectors (via phone or e-mail) when they are interested in participation in the study or when they have additional questions. Subsequent recruitment procedures are similar to the first recruitment stream.

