#### Primary hypothesis testing

The hypotheses related to the primary endpoint, parent-adolescent communication (PACS), will be analysed using a mixed model with the T1 measurement value for parent-adolescent communication as outcome variable and randomization group and baseline measure of parent-adolescent communication as predictor variables. Random effects that we will include in our mixed model are hospital and line of treatment. We will perform analyses on both intention-to-treat and per-protocol principles, with the intention-to-treat as the primary approach. In the intention-to-treat analysis, all participants who were enrolled and randomised will be accounted for in the main analysis, regardless of whether they completed the BOOST pACP program or not. The linear mixed models we intend to apply handle missing data through maximum likelihood estimation (i.e. assuming data is missing at random), so no missing data imputation should be applied. In case we do decide to apply multiple imputation, predictors for the imputation model will include the baseline measurement, randomization group, age and other possibly confounding variables (e.g. prognosis). In the per-protocol analysis, we will focus on families of which at least one parent was involved in all BOOST pACP conversations. During this analysis, we regard the family as a cluster because it is possible that during some conversation sessions both parents are present, while during others only one parent is present. Therefore, we will add the presence of parents during the conversation sessions as time-varying covariates.

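### The supportive per-protocol analysis selects families on session attendance, which only the intervention arm can have, and names no comparator; the primary intention-to-treat analysis is unaffected

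*Protocol article*

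**What the plan says.** All of the following is in the protocol article.

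- Primary hypothesis testing, on the status of the two analyses: "We will perform analyses on both intention-to-treat and per-protocol principles, with the intention-to-treat as the primary approach". The intention-to-treat set is every randomised family, whether or not it finished the programme.
- Same section, on the per-protocol set: "In the per-protocol analysis, we will focus on families of which at least one parent was involved in all BOOST pACP conversations". No counterpart for control families is given, and the section does not say with whom these families are compared.
- Same section, on the per-protocol model, after noting that one or both parents may be present at a given session: "Therefore, we will add the presence of parents during the conversation sessions as time-varying covariates".
- Same section, on the primary model: it has the "T1 measurement value for parent-adolescent communication as outcome variable and randomization group and baseline measure of parent-adolescent communication as predictor variables", with hospital and line of treatment as random effects. There is one outcome time point.
- Control: "The control group will not receive the BOOST pACP program".
- Recruitment procedures: families are told that "it is not obligatory for both parents to join all conversation sessions of the program", so incomplete attendance is foreseen. The section on discontinuing or modifying allocated interventions also allows withdrawal at any time.

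**The concern.** Attendance at every session is known only after randomisation and only in the intervention arm. If families who fall short are removed from that arm while their counterparts stay among the controls, the two groups are no longer comparable by design.

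The selection is plausibly related to the outcome. Sessions 1 and 3 are joint conversations between parent and adolescent, a participant in distress may stop, and PACS measures how well parent and adolescent communicate. Families who complete the series may communicate better anyway. A per-protocol estimate above the intention-to-treat estimate could then be read as showing that BOOST works when fully delivered, when some or all of the gap is selection.

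The session-presence covariate adds a second problem. It has no value for controls, so in a between-arm model it is entangled with the arm effect. It also varies over sessions, whereas the outcome is taken at T1 only, so a time-varying term has nothing to vary against. What the per-protocol arm coefficient estimates is therefore unclear.

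**Working it through.** **Inputs from the protocol article (Sample size).** Target difference 7 PACS points, SD 11.4, alpha 0.05, power 80%, 43 per arm, 90% retention, 96 families.

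**Reproducing the plan's figure.** Two-sided normal approximation: 2 × (1.96 + 0.84)² × (11.4/7)² = 41.6, so 42 per arm. The t-test solution is 42.6, so 43. Then 43/0.9 = 47.8, so 48 per arm and 96 in total. The stated size reproduces.

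**Inputs that are assumed, because the article gives none.** Completion proportion p (0.5 to 0.9), the T1 difference D between completers and non-completers with no programme effect (0.3, 0.5 or 0.8 SD, that is 3.42, 5.70 or 9.12 points), and the baseline-to-T1 correlation r (0.6). The comparator is assumed to be all controls.

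**Formula.** Completers exceed their whole arm by (1 − p) × D at T1. With D0 the corresponding difference at baseline and a regression slope of about r (equal SDs), the baseline-adjusted bias is about

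(1 − p) × (D − r × D0).

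Three cases follow:

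- Completion tracks T1, and baseline only through T1: D0 = rD, so the bias is (1 − p) × D × (1 − r²) = (1 − p) × D × 0.64.
- Completion tracks baseline and T1 equally, as a stable trait would: D0 = D, so the bias is (1 − p) × D × (1 − r) = (1 − p) × D × 0.4.
- Completion acts through baseline PACS only: D = rD0, so the bias is 0.

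Example at p = 0.7 and D = 5.70: the unadjusted bias is 0.3 × 5.70 = 1.71, and after adjustment it is 1.09, 0.68 or 0.

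**Simulation with no true effect** (43 per arm, SD 11.4, r = 0.6, ANCOVA on baseline, random effects left out):

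| p | Completion tracks | D (SD) | Bias by formula | Simulated bias | Rejection at nominal 5% |
|---|---|---|---|---|---|
| 0.7 | T1 | 0.3 / 0.5 / 0.8 | 0.66 / 1.09 / 1.75 | 0.6 / 1.1 / 1.8 | 5.5% / 8% / 12.5% |
| 0.7 | baseline and T1 equally | 0.3 / 0.5 / 0.8 | 0.41 / 0.68 / 1.09 | 0.42 / 0.71 / 1.14 | 5.0% / 6.1% / 8.1% |
| 0.8 | T1 | 0.3 / 0.5 / 0.8 | 0.44 / 0.73 / 1.17 | 0.4 / 0.8 / 1.2 | – |
| 0.8 | baseline and T1 equally | 0.3 / 0.5 / 0.8 | 0.27 / 0.46 / 0.73 | 0.27 / 0.48 / 0.71 | 5.4% / 5.4% / 6.4% |

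Repeat runs of the first row gave 5.4 to 6%, 8 to 8.6% and 12%. At p = 0.9, the formula for the largest gap (0.8 SD) gives 0.1 × 9.12 × 0.64 = 0.58 points, and rejection did not exceed 6% in these scenarios.

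**Second parameterisation.** Here completion correlates by rho with T1 after adjustment for baseline (3,000 runs per cell, r = 0.6).

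- rho = 0: bias about 0 and rejection about 5% at every completion rate.
- rho = 0.4: 1.75 points and 12.1% at 70% completion; 0.73 points and 5.8% at 90%.
- rho = 0.6, the most extreme value tried: 4.42 points and 45.4% at 50% completion; 1.07 points and 8.4% at 90%.
- Selection on baseline only (70% completion, correlation 0.5): bias −0.03 and rejection 4.7%.
- Intention-to-treat on the same data: about 5% in every cell.

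Baseline correlations of 0.3 and 0.77 gave similar rejection rates.

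**The case against.** The strongest reply is that nothing decisive rests on this analysis. Intention-to-treat is named as primary, covers all randomised families, and is what the sample size and the definition of success refer to. That stands: a reader might infer that the trial's main conclusion is at risk, and the article does not support that.

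A reader might also take it as written that completers are set against all controls. It is not; the section names no comparator. The whole control arm is the natural reading, because the criterion applied literally to both arms would leave no controls. Still, it is an inference, and a full protocol or analysis plan may settle it. What the article does fix is a one-arm criterion and a covariate that controls cannot have.

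A third tempting reading is that such an analysis shows an effect when there is none. That is too strong. If completion depends only on how well families communicated at baseline, adjustment for baseline PACS removes the bias. Even in the largest 70% scenario, about seven trials in eight would show no significant effect. Direction is not certain either: the criterion asks for only one parent, session 2a is for the adolescent alone and session 2b for the parents alone, and sessions may be missed through illness or treatment.

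Finally, the complier-average effect is not free of doubt. BOOST has ten components, and a family that does not complete may still have had booklets, the video and some sessions. If these help, the estimator credits their benefit to completers. This stands, and it is why the assumption must be reported with the estimate.

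**Conclusion.** The point holds for a supportive analysis. As defined, the per-protocol set selects on post-randomisation attendance that exists in one arm only, and the added covariate leaves the between-arm effect poorly defined. Against the whole control arm, the estimate is not protected by randomisation and can be biased, probably towards BOOST.

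At 70% completion, with completer gaps of 0.3 to 0.8 SD and a baseline correlation of 0.6, the bias is about 0.4 to 1.8 points, at most about a quarter of the 7-point target (1.8/7 = 0.26), with about 5 to 12% rejection. It is near zero if selection acts only through baseline PACS, small at 90% completion, and larger if completion is low and strongly tied to the outcome. Completion rate, gap, correlation and comparator are all assumptions. The change is worth making, but the primary result does not depend on it.

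**What to change.** **Effect in completers.** Estimate a baseline-adjusted complier-average causal effect by two-stage least squares, with randomised arm as instrument and completion as exposure, in all randomised families with T1 data. Non-compliance is one-sided because controls have no access to BOOST. Attendance can be taken from the diaries that facilitators fill in after each session (Data collection procedures). Define completion session by session, since session 2a has no parent in it.

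**Covariate.** Drop parental presence at sessions from the between-arm model. It can be described within the intervention arm.

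**If the per-protocol contrast is kept.** Name its comparator, label it supportive and non-randomised, and draw no efficacy claim from it.

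**Cost.** A change of wording and a few lines of R. The estimate is essentially intention-to-treat divided by p, so under no effect it stayed within 0.1 points of zero with about 5% rejection, but its interval is wider. With r = 0.6, the intention-to-treat standard error is about 11.4 × √(2/43) × 0.8 = 1.97. At 70% completion it becomes 1.97/0.7 = 2.81, so the 95% half-width grows from about 3.9 to 5.5 points.

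The method also assumes that partial attendance, booklets and video have no effect without completion. If non-completers gain t points, the estimate is too high by t × (1 − p)/p, which is 0.43t at 70% completion. State this assumption and report a version with number of sessions attended as the exposure as a sensitivity analysis.

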#### Secondary hypotheses testing

All secondary endpoints will be evaluated by testing the BOOST pACP program against the control group for each participant population separately (adolescents, parents and paediatric oncologists) with random effects being hospital and line of treatment.

For each of the primary and secondary endpoints, subgroup analyses will be performed using formal interaction tests to explore the extent to which the outcomes of the trial differ by gender, working situation and family situation of the parent(s) and gender and prognosis of the adolescent. Interaction terms between gender, working situation and family situation of the parent(s) and gender and prognosis of the adolescent on the one hand and the trial arms on the other hand will be added to the analysis models.

By including the baseline measurement as a predictor variable pre-existing differences will be controlled, enhancing the sensitivity of the analyses. Alpha is set at 0.05. To interpret the magnitude of the effects for the different outcomes, we will estimate effect sizes (Cohen’s d). Analyses will be conducted in IBM SPSS and R.

#### Process evaluation

Process evaluation of the implementation of the program will be analysed following the domains of Moore et al.’s MRC framework for process evaluations of complex interventions [26]: implementation, causal mechanisms and context, guided by pre-defined process indicators outlined in Additional file 2. Quantitative data collected via structured diaries (e.g. duration of an ACP conversation session) will be summarized by calculating frequencies and descriptive statistics (mean, median, standard deviation, range) using SPSS. All qualitative transcript data from interviews and audiotaped ACP conversations will be analysed by using thematic content analysis (i.e. deductive coding guided by the pre-defined process indicators, e.g. number of activities delivered as intended) and inductive coding into themes [45, 46]. The inductive approach will enable recognition of unexpected emergent themes. Qualitative data analysis will be managed in NVIVO. One researcher will read the transcripts carefully several times to have a sense of the data, with a 10% random sample of transcripts double coded by another researcher.

### Data monitoring

The main researcher ([name]) and data collectors will continuously monitor trial response using MS Excel sheets. An independent trial monitor will oversee the progress of the trial and ensure it will be conducted in accordance with the protocol and Good Clinical Practice standards. [name] will be the main contact person for participating hospitals to report problems or to ask questions regarding the trial. Data entry will be performed by the data collectors.

#### Harms

The research team is committed to minimizing risks of harm and maximizing the benefits for potential participants. Participation in this study could be emotionally stressful as it involves coming into contact with themes that might confront them with their illness, prognosis and expectations for the future. We have put in place a procedure to identify and handle any signal of distress in the adolescent or the parents. The facilitators guiding the ACP conversations are experienced psychologists by background. At the beginning of the ACP conversation sessions, the facilitator will explicitly tell the adolescents and parents that they can always take a break when needed or stop participation whenever they want to. In addition, the facilitator will refer participants to the psychologists at the involved paediatric oncology ward if they notice they may need support. In that case, the facilitator will coordinate the contact with the psychologist from the ward. The facilitator will let the research team know and keep into touch with the psychologist to discuss potential continuation or termination of the family’s participation and will add this information to the structured diary. Contact details of the psychologists of the ward and of the research team are mentioned on the informational materials.

## Discussion

We currently lack robust evidence regarding the effectiveness of advance care planning in adolescents (pACP) who have cancer and their parents which applies randomised controlled trial designs. This study aims to improve, via a novel program, both parent-adolescent communication about advance care planning themes and improved self-efficacy in talking about ACP themes with each other, by contributing to a more positive attitude. The BOOST pACP program is a multicomponent program consisting of three ACP conversation sessions between an external facilitator and the adolescent and their parent(s). In this structured ACP approach, broader ACP themes such as experiences of the disease, preferences for communicating, decision-making by the adolescent and expectations for the future are discussed – hence considering ACP to be relevant from diagnosis onwards and not only targeting the end of life [6, 24, 47]. Normalizing communication about ACP themes between parents and the adolescent may lead to improved communication with healthcare professionals and trigger a feeling of empowerment of the adolescents in their own care plan and future wishes. The effectiveness, implementation, contextual factors and causal mechanisms will be evaluated in adolescents (age 10–18) and their parent(s), applying a randomised controlled trial design and embedded mixed-methods process evaluation.

Several potential limitations to the study design have to be considered. Firstly, the limited use of validated questionnaires to evaluate our selected endpoints; validated measures regarding the outcomes related to communication that are targeted with these kinds of interventions are often non-existent [19, 48]. Options are to either select validated measurement instruments that match the intervention’s goals to a lesser extent and are therefore less relevant, or adapt existing measures matching the desired goals or impact of the intervention, while compromising on validity. After an extensive search and multiple deliberations within the research team, we decided on slightly adapting the PACS to the context of ACP and to construct items based on the Theory of Planned Behaviour [49] regarding our secondary endpoints. We have performed a thorough cognitive testing of the measurement instrument with the target group. Secondly, given our strict inclusion criteria, the number of adolescents with cancer meeting our inclusion criteria might be lower than expected, complicating reaching sufficient sample size for this trial. However, we intend to mitigate this limitation by recruiting adolescents via four hospitals and relevant support organizations.

Mixed-methods results of this study can inform future implementation of ACP in this distinct population. If effective, the BOOST pACP model could represent an ACP approach for paediatric oncology that may also apply to other areas in paediatric care and other paediatric populations with distinct serious illnesses.

## Trial status

Recruitment started in January 2021 and is expected to be finalized in January 2023.

## Data Availability

The datasets generated and/or analysed during the current study are available from the corresponding author on reasonable request.

## Abbreviations

ACP: Advance care planning
pACP: Paediatric advance care planning
PACS: Parent-adolescent communication scale
RCT: Randomised controlled trial
MRC: Medical Research Council
TIDieR: Template for intervention description and replication
AYA: Adolescents and young adults
SD: Standard deviation
